### Analysis

The power analysis is based on a pilot study in 38 patients in which FEV_1 _improved 14.9% ± 33.7 (mean ± SD) and 6 MWT distance improved 20.4% ± 41.5%. The samples size required to detect a 15% improvement in the treatment arm in FEV_1 _and a 17% improvement in 6 MWT distance at an alpha of 0.05 and a power of 0.90 is a minimum of 270 subjects with a 2:1 randomization to EBV procedure. Both of these values are above the threshold for minimal clinically important differences for these tests[17-19].

The study is designed as a superiority trial. For the two primary outcomes, the study is only considered a success if both endpoints show an improvement (one-sided test at p < 0.025). A one-sided test is appropriate to test for superiority. The actual probability of a false positive is lower than 0.025 given the imperfect correlation of the two endpoints. If change in FEV1 and change in 6 MWT were independent, the probability of a false positive would be 0.025*0.025 = 0.000625. In the pilot study generating the null hypothesis, the correlation coefficient between the change in FEV1 and 6 MWT was 0.3889. Given this r, the alpha for achieving a positive outcome is actually 0.005 (0.025*0.025^(1/(1+0.3889))). This is an assurance of avoiding a false positive well beyond convention.

The 2:1 randomization is chosen to enhance enrollment and increase the EBV population numbers in order to study covariates of treatment response. Although the 2:1 randomization increases the number of subjects required for the study, more robust subgroup comparisons may be possible.

For safety the 95% upper confidence interval for the Major Complication Composite rate delta between the EBV arm and the control arm is ≤ 30%.

The primary analysis cohort is intent to treat. As such, all 180 day missing data will be imputed using either a regression methodology if 30 and 90 day data are present or hot-deck imputation if there are not multiple datapoints available for a particular subject for regression analysis. Three unbiased imputations will be performed and the imputation resulting in the highest p-values will be selected as the final intent to treat dataset.

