The initial analysis will evaluate the mean percent change between EBV and control in FEV_1 _and 6 MWT using an unpaired t-test if data are normally distributed or Mann-Whitney-Wilcoxon test if data require non-parametric testing. To determine if covariates impact the primary outcome variables, and to adjust for potential imbalances in randomization, both primary endpoints will be further tested via a multivariate model (SAS PROC MIXED). In order to reduce the possibility of over-specification of the model, the potential covariates listed in Tables 6, 7, 8, 9 will be subjected to a univariate screening procedure similar to that described by Hosmer and Lemeshow[20]. Derivations for these variables are provided in Table 10. Main effects and interactions with a p-value of 0.15 or less are allowed to enter a multivariate analysis using a mixed linear model (SAS PROC MIXED). The treatment effect must remain in the model in order to substantiate the one-tailed test of superiority. Those variables found to have statistically significant interactions with the treatment arm via the mixed model analysis will be further analyzed in follow-on sub-group analyses. In order to limit the impact of multiple hypothesis testing, univariate sub-set analysis will be performed using only those independent variables that remain in the mixed model as interactions with the treatment arm. For those analyses performed on the remaining independent variables, appropriate adjustments will be made to account for impact on Type I error[11]. Secondary endpoint analyses will follow the same methodology as described above.

**Table 6 T6:** Plethysmography, spirometry and HRCT derived baseline potential covariates*

Variable	Plethysmography/Spirometry	HRCT at TLC	HRCT at RV	TLC and RV HRCT ^†^
RV	X			
RV % Predicted	X			
TLC	X			
TLC % Predicted	X			
RV/TLC	X			
VC	X			
FVC	X			
FVC % Predicted	X			
FEV_1_	X			
FEV_1 _% Predicted	X			
FEV_1_/FVC	X			
Destruction Score of Target Lobe		X	X	
Ipsilateral Heterogeneity^††^		X	X	
Whole Lung Heterogeneity^††^		X	X	
For RUL Treatment Subset only: RUL-RML Heterogeneity^††^		X	X	
Target Lobe Volume % of TLC		X		
Target Lobe Volume % of RV			X	
Max Destruction Score other than target		X	X	
Min Destruction Score other than target		X	X	
Target Lobe Destruction Score % TLC-RV Delta				X
Target Lobe Volume % TLC-RV Delta				X
Fissure Score^†††^		X		

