Advanced emphysema is characterized by destruction of lung parenchyma and augmentation of anatomic connections for air passage between adjacent lung lobules. Unfortunately for endobronchial lung volume reduction procedures, these collateral communications may traverse lobar fissures [25]. These peripheral communications between lobes then may allow for continued lobar ventilation despite completely occluded lobar airways. Because this collateral ventilation is not easily quantified by current detection methods, the outcome of EBV valve placement may be heterogeneous. Ultimately, secondary analyses will include responder analysis, in order to determine the proportion of patients with clinically meaningful responses.

Given the complex mechanical and gas exchange consequences of valve insertion, it is possible that the magnitude of volume reduction in a lobe may not be associated with changes in other meaningful physiologic or functional indices following the procedure. For example, the impact of valve placement on symptoms associated with dynamic hyperinflation or variations in gas exchange utilizing collateral channels may be associated with clinical improvements independent of changes in conventional resting pulmonary tests. The composite primary endpoint was chosen to include a functional exercise measure to capture such changes.

Ultimately, the future of the EBV valve will be determined by the balance between efficacy and safety. Since the valves are removable for mild or moderate adverse events, valve safety will be impacted by the frequency of severe adverse events that might affect survival in a compromised patient population. In fact, individuals who demonstrate improvements in lung function may also demonstrate an increase in exacerbation frequency. For this reason, quality of life indices including the Quality of Well Being Scale and the Saint George's Respiratory Questionnaire are considered integrative parameters which can determine the balanced impact of the intervention [26,27]. One strategy to minimize overall adverse response would be to remove valves earlier in the patients who do not have clinically important responses. If a meaningful outcome is measurable in the first few days after the procedure, future alternative targeting strategies might be employed to determine response at earlier times after randomization.

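### Keeping whichever of three imputations has the highest p-values pulls the estimate towards no effect, makes intervals too narrow, and does not identify one dataset for two co-primary endpoints

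*Protocol article*

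**What the plan says.** All of this is in the Analysis section of the protocol article.

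- Cohort: "The primary analysis cohort is intent to treat".
- Missing values: "all 180 day missing data will be imputed using either a regression methodology if 30 and 90 day data are present or hot-deck imputation", the latter for patients without enough earlier data points.
- Choice of dataset: "Three unbiased imputations will be performed and the imputation resulting in the highest p-values will be selected as the final intent to treat dataset".
- Success rule: "the study is only considered a success if both endpoints show an improvement (one-sided test at p < 0.025".
- Tests on the completed data: "using an unpaired t-test if data are normally distributed or Mann-Whitney-Wilcoxon test if data require non-parametric testing", followed by a mixed model. Secondary endpoints follow the same method.

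Nothing in the article pools the three imputations or adds between-imputation variance. It does not say what happens when the two endpoints point to different imputations, or which test's p-value drives the choice.

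**The concern.** The rule appears to be meant as a safeguard, and it is stated as the primary-analysis rule rather than left to a later document. It has two faults.

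(a) Each imputation may be unbiased on its own, but the one picked for its high p-value is not. It is the least favourable of three random draws. Because it is analysed as observed data, its standard error reflects 270 real values when some were filled in. The reported effect is too small and its interval too short.

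(b) Success needs both FEV1 and six-minute walk (6MWT), yet the rule speaks of one dataset. If FEV1 has its highest p-value in one imputation and 6MWT in another, the text does not say which to use, so the analyst would choose after seeing the results.

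At stake are the size and precision of the main efficacy results, some power, and whether a second analyst could reproduce the primary dataset.

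**Working it through.** The plan gives no figure for the effect of this rule, so there is none to reproduce. I first check the set-up against the sample-size statement.

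**Inputs from the Analysis section.** Pilot results: FEV1 and 6MWT "improved 14.9% ± 33.7 (mean ± SD) and 6 MWT distance improved 20.4% ± 41.5", so SDs of 33.7 and 41.5, taken for both arms. Effects: "detect a 15% improvement in the treatment arm in FEV_1 _and a 17% improvement in 6 MWT distance", taken as between-arm differences. Correlation of the two changes 0.3889. At least 270 patients at 2:1, so 180 and 90. One-sided 0.025 per endpoint.

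**Assumptions not in the document.** 10, 20 or 30% missing completely at random; imputation within arm; for regression, a correlation of 0.6 between early and day-180 values and a random residual.

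**Step 1, no missing data.** SE = SD × √(1/180 + 1/90) = SD × 0.1291.
- FEV1: 33.7 × 0.1291 = 4.35; 15/4.35 - 1.96 = 1.49; power about 0.93.
- 6MWT: 41.5 × 0.1291 = 5.36; 17/5.36 - 1.96 = 1.21; power about 0.89.

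Both are close to the stated 0.90, so the set-up is a fair reading of the plan.

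**Step 2, bias by hand.** With hot deck and missing fraction m, estimates differ between imputations with SD = SE × √m. The lowest of three normal draws lies on average 3/(2√π) = 0.846 SDs below the mean. FEV1 bias is therefore about -0.846 × 4.35 × √m:
- m = 0.10: -0.846 × 4.35 × 0.316 = -1.2
- m = 0.20: -0.846 × 4.35 × 0.447 = -1.6
- m = 0.30: -0.846 × 4.35 × 0.548 = -2.0

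Regression with r = 0.6 multiplies these by √(1 - 0.36) = 0.8, giving -0.9, -1.3 and -1.6.

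**Step 3, coverage by hand.** The selected estimate has variance of about SE² × [1/(1 - m) + 0.559m], where 0.559 is the variance of the lowest of three standard normal draws. At m = 0.20 this is 4.35² × (1.25 + 0.112), an SD of 5.08 against a reported SE of about 4.35. The 95% half-width is 1.97 × 4.35 = 8.57. Coverage is Φ((8.57 + 1.65)/5.08) - Φ(-(8.57 - 1.65)/5.08) = 0.978 - 0.087 = 0.89.

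**Step 4, simulation.** Three imputations per trial, keeping the highest p-value for each endpoint:

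| | 10% | 20% | 30% |
|---|---|---|---|
| FEV1 bias, hot deck (true 15) | -1.1 | -1.6 | -2.0 |
| FEV1 bias, regression | -1.0 | -1.3 | -1.6 |
| 6MWT bias, hot deck (true 17) | -1.4 | -1.9 | -2.5 |
| FEV1 coverage, hot deck | 0.92 | 0.89 | 0.85 |
| FEV1 coverage, regression | 0.93 | 0.91 | 0.89 |
| Power for both endpoints, hot deck | 0.73 | 0.67 | 0.61 |
| Power for both, observed cases only | 0.79 | 0.73 | 0.66 |

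These match the hand calculation. One-sided error per endpoint is about 0.02 to 0.03 throughout. With regression, power for both endpoints is about 0.75/0.70/0.66, so the loss against observed cases is smaller and vanishes at 30%.

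**Step 5, does the rule name one dataset?** If the imputed values for the two endpoints were unrelated, the same imputation would be worst for both one time in three. Simulated agreement is 33 to 35% with regression and 47 to 49% with hot deck when one donor supplies both values. In roughly half to two thirds of trials the rule therefore identifies no single dataset.

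**Step 6, pooling instead.** Twenty hot-deck imputations combined by Rubin's rules gave FEV1 bias between -0.15 and +0.19 points, coverage of 94.4 to 96.3% and one-sided error of 0.024 to 0.030.

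**The case against.** The best defence is that the rule is fixed in advance and works against the device. That stands. It lowers the estimate and power and cannot readily produce a false success.

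A reader might infer that heavy missingness makes the rule anti-conservative, since per-endpoint error nears 0.03 at 30% missing. That is not supported. Pooling by Rubin's rules gave a similar range, and because both endpoints must succeed, the false-positive rate with no effect on either is below 0.01.

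It is also fair that the document gives no missing rate, and that hot deck is reserved for patients without usable early data, so the all-hot-deck figures are the upper end. At 5% missing, FEV1 bias is about -0.8 points and coverage about 0.93. If the regression adds no random residual, the three versions coincide for those patients and selection has nothing to act on, but the variance is understated further. Drawing donors from both arms would bias the estimate more, but the article does not say this is done, and describing the imputations as unbiased argues against it.

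The article names no efficacy confidence interval, so the coverage figures concern whatever interval is reported from the selected dataset.

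Finally, a reader might infer that patients who die before day 180 are credited with a predicted gain. The imputation wording has no exception for deaths, and the Discussion foresees "severe adverse events that might affect survival in a compromised patient population", but that remark concerns valve safety. The article does not say that deaths are imputed, and the full protocol may settle it. This is a question to answer, not an established error.

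**Conclusion.** The point holds for estimation, coverage, power and reproducibility, and does not hold as a claim of excess false positives. Followed as written, the rule understates the FEV1 effect by about 1 to 2 points of 15 at 10 to 30% missing, lets nominal 95% intervals cover about 85 to 93%, and with hot deck costs about 5 to 6 points of joint power (for example 0.79 - 0.73 = 0.06). These sizes rest on assumed missing rates, data missing completely at random, imputation within arm and, for regression, an assumed correlation of 0.6. With few missing values they are small.

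The ambiguity over which dataset is meant does not depend on the size of the missing rate. It arises whenever the three imputations differ and there are two endpoints. Any apparent protection of the error rate comes from two faults roughly cancelling, a downward selection and an understated variance, and how well they cancel depends on a missing rate nobody knows in advance.

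**What to change.** Replace the selection sentence. Use multiple imputation within each arm, from baseline, 30-day and 90-day values and the randomisation strata, and combine all sets by Rubin's rules. This gives one estimate, interval and p-value per endpoint, with no choice between datasets. A repeated-measures mixed model on all visits is an alternative. If a deliberately pessimistic analysis is wanted, keep it as a labelled sensitivity analysis.

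As a secondary point, state whether the day-180 values to be imputed include those of patients who died before that visit, and add a sensitivity analysis that does not impute a day-180 gain for them. The exact rule for deaths is the sponsor's choice.

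The cost is revised wording and slightly more programming. The 30- and 90-day assessments are already scheduled, so no new data are needed.

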## Methods

### Overview

VENT is a two-arm, randomized, controlled, multi-center trial designed to study the safety and efficacy of the EBV implantation procedure, and the ability of the EBV to produce sustained improvement of symptoms in emphysema. The study sample size was a minimum of 270 subjects with heterogeneous emphysema, with randomization at a ratio of 2 to 1 (*i.e., *two patients were randomized to the study device treatment arm for every one randomized to the control group).

Given the similarity in intended treatment effect between LVRS and EBV implantation, combined with a goal of allowing easy comparisons between the results of the NETT and VENT, the VENT design largely followed that of the NETT. The inclusion/exclusion criteria were similar and both studies required pulmonary rehabilitation prior to randomization in order to maximize function prior to intervention. Both studies allowed treatment of the upper or lower lobes based on CT analysis; however, the NETT required bilateral (left and right lung) treatment whereas VENT treatments were unilateral only. Patient randomization in VENT was stratified per the subgroups identified in the NETT according to lung treatment region (upper versus lower) and post rehabilitation pre-treatment exercise capacity (low versus high).

In addition, the VENT study design conformed to the consensus recommendations of an independent panel of physician specialists convened by the U.S. Food and Drug Administration in February of 2003 to provide study design input for emerging bronchoscopic treatments for emphysema[10]. Questions considered at the panel included appropriate control groups, safety assessment, appropriate outcome metrics, and length of follow up.

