### Primary outcome measures

The co-primary effectiveness endpoints are the mean percent change in both forced expiratory volume in one second (FEV_1_) and distance traveled in the six minute walk test (6 MWT) in the treatment group (EBV implantation) as compared to the control group (optimal medical management) at 180 days after randomization. The primary safety endpoint is a comparison of major complications between the two groups over the initial follow-up period of 180 days. Additionally, patients will be followed for up to 3 years post randomization for long term safety assessment.

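### The co-primary endpoints are mean differences, but the initial test may become a rank test depending on the data, and no adjusted analysis with fixed covariates is pre-specified

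*Protocol article*

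**What the plan says.** **Endpoint.** Under Primary outcome measures: "The co-primary effectiveness endpoints are the mean percent change in both forced expiratory volume in one second" and in six-minute walk distance, EBV against control, at 180 days. Table 1 repeats this.

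**Sizing.** The Analysis section works from pilot means and standard deviations: FEV1 "improved 14.9% ± 33.7 (mean ± SD) and 6 MWT distance improved 20.4% ± 41.5" percent. It states that the number needed at "an alpha of 0.05 and a power of 0.90 is a minimum of 270 subjects with a 2:1 randomization to EBV procedure".

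**Success rule.** In the same section, "the study is only considered a success if both endpoints show an improvement (one-sided test at p < 0.025".

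**Initial test.** The arms are compared "using an unpaired t-test if data are normally distributed or Mann-Whitney-Wilcoxon test if data require non-parametric testing". This test has no covariates and no stratification.

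**Randomisation.** The Overview says "Patient randomization in VENT was stratified per the subgroups identified in the NETT according to lung treatment region (upper versus lower" and names low or high exercise capacity after rehabilitation as the second factor.

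**Later model.** The Analysis section then tests both endpoints again in SAS PROC MIXED, partly to correct chance imbalance. Baseline FEV1 (Table 6), baseline six-minute walk (Table 7) and the NETT strata (Table 8) are candidates. A candidate enters if its univariate p-value is 0.15 or less. The treatment effect has to stay in this model for superiority to be supported.

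**Expected response.** Because of collateral ventilation, the Discussion says "the outcome of EBV valve placement may be heterogeneous", and it plans a responder analysis.

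**The concern.** Two features of the primary comparison are poorly fixed.

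First, the endpoint and sample size are stated in means, but the observed distribution decides whether the initial test addresses means. Mann-Whitney-Wilcoxon asks whether a value from one arm tends to exceed a value from the other. That is a statement about means only if one arm's distribution is a shifted copy of the other's. If some patients respond strongly and others hardly at all, the EBV arm will differ in shape as well as location. The rank test can then miss a real mean gain, or reject when the means are equal.

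Second, randomisation was stratified, and baseline FEV1 and walk distance are measured beforehand, but none of these has a guaranteed place in the analysis. Ignoring the stratification factors tends to overstate the standard error. Ignoring a prognostic baseline value gives up precision. In the screened model these variables compete with others that arise after randomisation and exist only in the EBV arm: valve expectoration (Table 7), and target-lobe atelectasis and lobar exclusion at day 180 (Table 9). The adjusted model is therefore not known until the data have been searched.

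**Working it through.** **1. The plan's own figures.** Inputs from the Analysis section: differences 15 (FEV1) and 17 (walk), SDs 33.7 and 41.5, two-sided 0.05 (one-sided 0.025), power 0.90, 2:1 allocation.

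Control-arm n = 1.5 × (1.960 + 1.282)² × (SD/difference)².

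- FEV1: 1.5 × 10.51 × 5.05 gives 80, total 240.
- Walk: 1.5 × 10.51 × 5.96 gives 94, total 282.

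Neither equals 270. That is a separate sample-size matter and carries no weight here. At 180 and 90 patients the standard error is SD × √(1/180 + 1/90) = SD × 0.1291:

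- FEV1: 15/4.351 = 3.448; Φ(3.448 − 1.960) = 0.932.
- Walk: 17/5.358 = 3.173; Φ(3.173 − 1.960) = 0.887.
- Both, bivariate normal with the article's r = 0.3889: 0.840.

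**2. Behaviour of the t-test and the rank test.** Simulations at 180/90, one-sided 0.025. The article gives no control SD, responder fraction or normality criterion, so the distributions are assumptions, as is the switching rule (Shapiro-Wilk at 0.05). In the responder mixes the EBV mean is 15 and its SD about 33.5 to 36; controls have mean 0 and the same within-group noise.

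| Assumed EBV distribution | Normality rejected | t-test power | Rank power |
|---|---|---|---|
| 20% gain 75, rest 0 | 100% | 0.98 or more | about 0.77 |
| 30% gain 50, rest 0 | about 39% | 0.98 | 0.94 |
| 20% gain 50 above a general shift of 5 | about 35% | 0.97 | 0.93 |
| 40% gain 37.5, rest 0 | about 6% | 0.97 | 0.95 |
| 50% gain 30, rest 0 | about 5% | 0.95 | 0.94 |

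Three further cases:

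- **Normal data, common SD.** Type I error is 0.023 (t), 0.024 (rank) and 0.023 (switched). Power is 93.1%, 91.8% and 93.1%.
- **Lognormal data, equal shape, shifted.** Power is 92.0% for the t-test and 99.5% for the switched procedure.
- **Equal means, different shapes.** 80% of EBV patients gain 10 and 20% lose 40, noise SD 15. The mean is 0.8 × 10 − 0.2 × 40 = 0, equal to control. The rank test rejects in about 27% of trials; the Welch test stays at about 2 to 3%.

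A comparison of means with unequal-variance standard errors thus keeps close to its nominal level at this size without a normality condition.

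**3. Value of fixed adjustment.** If baseline and strata have multiple correlation ρ with percent change, the residual variance is multiplied by 1 − ρ², so each ratio in step 1 is divided by √(1 − ρ²). The article does not give ρ. The r of 0.3889 is kept for the joint figure.

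| ρ (assumed) | FEV1 | Walk | Both |
|---|---|---|---|
| 0 | 0.932 | 0.887 | 0.840 |
| 0.1 | 0.934 | 0.890 | 0.845 |
| 0.2 | 0.940 | 0.899 | 0.86 |
| 0.3 | 0.951 | 0.914 | 0.88 |
| 0.4 | 0.964 | 0.933 | 0.91 |
| 0.5 | 0.978 | 0.956 | 0.94 |

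**The case against.** A reader might infer that the plan ignores baseline and the strata altogether. It does not. The PROC MIXED analysis covers both endpoints, lists these variables as candidates and makes the superiority conclusion depend on the treatment effect staying in the model. So a rank test result does not settle success alone, and it goes too far to say that the data choose the whole success criterion. What stands is that neither baseline nor strata are fixed in advance in any analysis.

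A reader might also infer that the switch loses power, and that it will almost certainly be triggered. The article says only that response may be heterogeneous. The 20-point loss belongs to one extreme mix; in the milder mixes normality is often not rejected and the loss is 1 to 4 points. Under normality the switch costs essentially nothing, and for a skewed shift of equal shape it gains. If the arms have identical distributions, the rank test holds its level. The excess rejections concern equal means with unequal shapes.

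Omitting stratification factors makes a test conservative, not invalid. The gain from adjustment could be slight, since percent change already divides by baseline.

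Finally, an analysis plan not shown may define the normality criterion. That would say when to switch. It would not make the rank test a test of the stated mean endpoint, and the article itself fixes the conditional rule.

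**Conclusion.** The concern holds in a limited form. The stated endpoint is a mean difference, and the initial test addresses it only if the data look normal or the arms differ by a pure shift. The Discussion gives reason to doubt the latter. The consequence has no single size or direction: under the assumed distributions it runs from a gain in power, through losses of 1 to 4 points, to a loss of about 20, with about 27% rejection in one equal-means case.

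Baseline and strata are left out of the initial test only. Afterwards they depend on a p ≤ 0.15 screen shared with post-randomisation variables, so there is no pre-specified adjusted analysis. Fixing them would raise joint power at 270 from 0.84 by about half a point at ρ = 0.1 and about ten points at ρ = 0.5. This assumes the pilot SDs apply to both arms and that the correlation between the two test statistics is 0.3889. The plan is not invalid on this account, but the change is worth making.

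**What to change.** Remove the normality condition. For each co-primary endpoint, pre-specify one primary analysis: a linear model of percent change at 180 days on arm, the baseline value of that measure and the randomisation strata (treatment region by exercise capacity). Use heteroscedasticity-consistent standard errors and test the arm effect one-sided at 0.025, with both endpoints required as now.

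Keep the unpaired t-test and a stratified Mann-Whitney-Wilcoxon test as sensitivity analyses that do not decide success. Keep the screened PROC MIXED model as exploratory work on predictors of response, and detach the superiority requirement from it.

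The cost is analysis wording only. Table 2 shows that spirometry, walk test, cycle ergometry and CT are all obtained before randomisation, so no visit, measurement or patient is added.
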